### Sample size and Justification

A preliminary study showed the intra class correlation for the self-efficiency measure among schools was 6.5%. In the cluster randomised design with an average of 20 students available in each school, to detect a half standard deviation difference in means of 4 points (i.e. between 49.6 and 53.6 with SD = 8.1) at the 5% level of significance with 80% power, approximately 17 schools and 340 students in total would be required [25]. The intra class correlation for BMI measure is 0.6%, therefore to detect the half standard deviation difference of 2.3 BMI change at 5% level of significance with 80% power would require 8 schools and 160 students in total. Assuming an overall 10% drop-out rate of students and potential school withdraw, for self-efficiency measure, a total of 396 students with a mean of 22 per school for 18 schools would be required in this study.

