### Statistical Analysis

The outcome data present a 3-level hierarchical structure due to the cluster randomisation and follow-up design, i.e. students (level 2 unit) nested within schools (level 3 unit) and repeated measures at 3 time points (level 1 unit) are nested within students. Treatment status is school level variable, together with some student level variables such as gender, age and other background variables. Multilevel modelling will be applied to examine the treatment effects on the primary outcome measures [26], taking into account variability of outcomes between school and between students. The student's weight category (overweight at baseline if =>91^st ^centile) and status of having asthma (yes/no) could also be included in the model as student level (level 2) exploratory variables. The intervention effects in the outcome measure differentiated by these group of students will be tested in the multilevel models analysis. Since both primary outcomes are continuous variable, multilevel linear models will be considered. The computational algorithm in multilevel modelling takes care of missing outcome automatically under missing at random (MAR) assumption. However, we shall examine missing value pattern by multilevel logistic regression to make sure missing data are not dependent on key variables such as deprivation or overweight. Sensitivity analyses will be performed if missing data are not missing at random.

Analyses for secondary outcome variables will be conducted in similar manner.

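### The planned missingness check tests MCAR rather than MAR, so it cannot serve as the trigger for sensitivity analyses

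*Protocol article*

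**What the plan says.** Three consecutive sentences in the protocol article, Statistical Analysis, make up the missing-data rule.

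- Assumption: the multilevel algorithm "takes care of missing outcome automatically under missing at random (MAR) assumption".
- Check, introduced as a reservation about that assumption: a multilevel logistic regression of the missing-value pattern "to make sure missing data are not dependent on key variables such as deprivation or overweight".
- Trigger: "Sensitivity analyses will be performed if missing data are not missing at random".

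The same section describes the outcome model as three-level, with measurements at three time points within pupils within schools. Covariates are given loosely. Treatment is named "together with some student level variables such as gender, age and other background variables". On weight and asthma the text is permissive: "The student's weight category (overweight at baseline if =>91^st ^centile) and status of having asthma (yes/no) could also be included in the model". Deprivation is not named as a covariate. The section on sample size plans for loss as follows: "Assuming an overall 10% drop-out rate of students and potential school withdraw".

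**The concern.** Read in order, the second sentence tests the assumption in the first and decides whether the third applies. The test does not match the assumption. Deprivation and overweight are observed (I read overweight as baseline status, which is how the section defines it). A link between missingness and an observed variable is what MAR permits. What MAR excludes is a remaining link with the unseen 12-month BMI or ESE.

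Two misreadings are then possible. A regression that finds nothing could be taken as support for MAR, and no sensitivity analysis would follow. A regression that finds dependence could be taken as failure of MAR, when the remedy is to condition on the variable found. Whether robustness to dropout is examined at all would rest on a judgement that the data cannot settle.

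**Working it through.** The document states no figure on this point, so the main check is of the logic.

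**1. Definitions.** MCAR: missingness depends on nothing, observed or unobserved. MAR: it may depend on observed data. MNAR: it depends on unobserved values even after conditioning on the observed data.

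**2. The rule under each mechanism.** This assumes that the regression result is what decides the trigger.

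| True mechanism | Regression on deprivation and overweight | Rule leads to | What is needed |
|---|---|---|---|
| MCAR | Nothing, bar chance | No sensitivity analysis | Nothing further for bias |
| MAR, through deprivation or baseline overweight | Dependence | Sensitivity analyses | Condition on that variable |
| MNAR, unrelated to those variables | Nothing, bar chance | No sensitivity analysis | Sensitivity analysis |
| Both MAR and MNAR components | Dependence | Sensitivity analyses, set off by the MAR component | Both |

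The first and third rows give the same regression result, so it cannot separate the case that needs a sensitivity analysis from the case that does not.

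**3. Size, as illustration only.** Let p be the proportion missing in an arm and delta the mean departure of its missing values from the MAR prediction. The shift in the arm difference is p(I) × delta(I) − p(C) × delta(C). Inputs from the section on sample size: 10% loss (taken as equal in both arms), ESE SD 8.1 and target 4, and BMI target 2.3 described as half an SD, hence SD 2 × 2.3 = 4.6. Assumed: delta, in the intervention arm only.

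- ESE, delta = 2: 0.10 × 2 = 0.20 points.
- ESE, delta = 4: 0.10 × 4 = 0.40 points.
- ESE, delta = 8.1 (one SD, extreme): 0.10 × 8.1 = 0.81 points; 0.81/4 = 20% of the target.
- BMI, delta = 4.6 (one SD, extreme): 0.10 × 4.6 = 0.46 kg/m²; 0.46/2.3 = 20% of the target.

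The MAR prediction already uses the child's earlier values, so the natural scale for delta is the residual SD, SD × √(1 − r²), where r is the correlation with earlier measurements. The document does not give r. Assuming a range for ESE:

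- r = 0.4: 8.1 × 0.917 = 7.42; shift 0.74.
- r = 0.6: 8.1 × 0.8 = 6.48; shift 0.65.
- r = 0.8: 8.1 × 0.6 = 4.86; shift 0.49.

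**4. Simulation of the check.** 1,500 null trials per mechanism, 18 schools × 22 pupils, SD 8.1 and intraclass correlation 0.065 (from the document). Assumed: 33% overweight, overweight children 3 points lower, r = 0.6, dropout log-odds slope 1.2. Analysis: single-level complete-case estimate adjusted for baseline and overweight, with an ordinary logistic check on overweight.

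- Dropout through baseline overweight only (MAR, about 11% missing): the check fires in 96% of trials; bias 0.02 points (Monte Carlo SE 0.02), so none.
- Dropout in intervention schools through the unseen follow-up residual (MNAR, 12.7% against 8.3% missing, 10.5% overall): the check fires in 4%, its chance rate; bias 0.81 points.

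The second scenario is severe: 0.81/0.127 implies a delta of about 6.4 points, close to one residual SD at r = 0.6. A check that included arm might notice the unequal loss, but unequal loss is not in itself evidence of MNAR.

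**The case against.** The case on the other side has real force in five places.

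- **Sensitivity analyses are foreseen.** A reader might infer that informative dropout will go unexamined. The text does not support that. It commits to looking at missingness and to sensitivity analyses under a condition, and they may well run, if for the wrong reason. What stands is that nothing assures it.
- **The planned model already does much of the work.** Baseline and 4-month values are responses in the repeated-measures likelihood. Dropout related to earlier BMI is therefore handled in the BMI model, and dropout following a fall in ESE seen at 4 months is handled in the ESE model. Only change that the observed values do not predict is MNAR. This limits the size but does not repair the trigger. The ESE model conditions on weight status only if that covariate is included.
- **The covariate list is open.** A reader might infer that the plan ignores deprivation. It may fall under the other background variables, and it is a factor in matching schools into pairs. Effects by weight category and asthma are to be tested. The text permits conditioning on these variables but does not tie it to what the regression finds.
- **The magnitudes rest on assumptions.** A one-SD departure confined to one arm is extreme, and the document plans for 10% loss, not more. The simulation does not use the planned three-level model. It shows how the check behaves and is no forecast for this trial.
- **Detail may sit in an analysis plan that is not shown.** That covers the choice of sensitivity method and its range. It does not cover a rule that the article prints and that does not work as printed.

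**Conclusion.** The point holds in limited form. The rule checks a condition that MAR does not require, and makes sensitivity analyses depend on a state that observed data can neither establish nor exclude. It can fire when the MAR model is valid and stay silent when it is not.

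A reader might go further and conclude that the primary analysis is biased or that the trial's conclusion is at risk. The documents do not support that. A likelihood-based multilevel model under MAR is a sound primary analysis, and nothing in the article shows that dropout will be MNAR. With equal 10% loss and a departure in one arm only, the shift is about 0.10 × delta: 0.2 to 0.4 ESE points for delta of 2 to 4, and about 0.8 for an extreme delta of one SD, against a planned 4. This should be fixed before outcome data are seen. It has no bearing on the sample size.

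**What to change.** 1. Delete the conditional trigger. State that a sensitivity analysis for departures from MAR will always be run for both primary outcomes at 12 months. A delta-adjusted or pattern-mixture analysis would serve, with delta allowed to differ by arm over a stated range scaled to the residual SD given earlier measurements. The exact range can be left to the analysis plan.
2. Keep the logistic regression but change its purpose: it identifies predictors of missingness. State that those found (for example deprivation, baseline weight status, asthma) will enter the multilevel model or a multilevel imputation model. An outcome's own baseline and 4-month values need not be added as covariates, because they are already responses in the likelihood. Adding them would use the same measurement on both sides of the model.
3. Do not describe a regression that finds no dependence as evidence for MAR.

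The cost is a few sentences and a little more analysis work. No new data are needed.

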### Ethics

The study received ethical approval from The University of Nottingham Medical School Ethics Committee (B/10/2009) and is currently recruiting participants.

## Discussion

Results from the study will show whether a targeted activity intervention is effective and feasible. Outputs from the study will include a fully developed intervention with supporting materials.

## List of abbreviations

BMI: Body Mass Index; CBIS: Child Body Image Scale; CLAHRC: Collaborations for Leadership in Applied Health Research and Care; CSSAPA: Children's Self-Perceptions of Adequacy in and Predilection for Physical Activity scale; DoH: Department of Health; NDL: Nottinghamshire, Derbyshire, Lincolnshire; PAQ: Physical Activities Questionnaire; RCT: Randomised Control Trial; SDQ: Strengths and Difficulties Questionnaire.
